## Abstract

Radiographer commenting systems have not been successfully implemented in many Australian hospitals, despite evidence of their benefit and adoption elsewhere, such as the United Kingdom. An important contributor to the lack of widespread adoption of radiographer commenting in Australia (and likely elsewhere) is the limited availability of accessible education options for radiographers. The purpose of this randomised controlled trial is to compare the effectiveness of the same image interpretation education program delivered over an intensive 2‐day period (intensive format) versus a series of shorter regular workshops (non‐intensive format). The study design is a multicentre, stratified (by years of experience) two group parallel‐arm single‐blind (assessor blinded) randomised controlled trial. Participants will be allocated to one of the two groups: (1) intensive format of education or (2) non‐intensive format of education in a 1:1 ratio. Participants will undergo assessments before education, at 1 week post‐intervention completion and at 12 weeks post‐intervention completion. Findings from this trial will be of relevance to radiographers seeking image interpretation training as well as organisations providing image interpretation education to prepare clinical staff for participation in a radiographer commenting system. A limitation of the trial is that the sample will be inclusive of radiographers, and findings may not be able to be directly extrapolated to other clinical disciplines (e.g. junior doctors, physiotherapists or nurse practitioners).

## Background

Access to appropriate and timely medical imaging is important for the provision of effective emergency healthcare in hospital settings.^1^, ^2^ Findings from medical imaging investigations underpin many diagnostic and treatment decisions, particularly for people who have presented to hospital following a trauma event. Even with the rise in use of computed tomography since its development in 1972,^3^, ^4^ radiographic image series remains the primary imaging modality requested for patients who may have sustained trauma.^5^

In emergency settings, the definitive radiology report may not be available within a clinically relevant timeframe.^2^ This means that treatment decisions are likely to have been implemented by the referring clinical team before the radiologist's report is available in many cases. Unfortunately, delay between radiographic image capture and the availability of the radiologist's report can contribute to missed, incomplete or incorrect diagnoses.^2^, ^6^, ^7^ One approach to mitigate risk and better support junior or inexperienced members of the referring clinical team is the recording of a brief comment by the radiographer at the time of image capture to highlight any abnormalities they may have detected.^8^, ^9^, ^10^, ^11^

It has been suggested that radiographer commenting that highlights and describes acute abnormalities at the point of care may enhance patient management in hospital emergency departments.^10^, ^12^, ^13^, ^14^ However, this enhancement is dependent on radiographers' ability to detect and describe abnormalities when viewing and interpreting trauma radiographs. Importantly, radiographer performance in this regard can be improved as a result of targeted education in image interpretation.^15^, ^16^, ^17^, ^18^

A radiographer commenting system has not been successfully implemented in many Australian hospitals, despite evidence of its benefit and adoption elsewhere, such as the United Kingdom.^10^, ^13^, ^19^ An important contributor to the lack of widespread adoption of radiographer commenting in Australia (and likely elsewhere) may by the limited availability of accessible and effective training options for radiographers.^11^ Two key factors limiting access to appropriate education are likely to include the availability of suitably qualified experts to deliver image interpretation education and the ability of radiographers from geographically diverse locations to access it.

A potential solution to facilitate the accessibility of training is to offer different formats of education delivery that can be potentially flexible with radiographers' schedules. In preparation for the present trial, two specific formats for delivery of a short‐course image interpretation education program for radiographers were considered. The two formats include the same educational content delivered at different intensities by the same facilitators. One approach includes an intensive delivery 2‐day training suitable for radiographers who may require the training to be completed in a short amount of time (e.g. a rural radiographer travelling to a metropolitan centre or radiographers who can only complete training on days away from clinical work). The other approach is a non‐intensive delivery of short regular workshops that may have potential to be incorporated into regular hospital in‐service education programs. Although prior studies involving imaging interpretation among radiographers have been promising,^8^, ^9^, ^12^, ^16^ to date, there is no study that has compared the accuracy of radiographer image interpretation for skeletal X‐rays from radiographers who have received different formats of an educational intervention.

The purpose of this randomised controlled trial is to compare the effectiveness of the same image interpretation education program delivered over an intensive 2‐day period (intensive format) versus a series of shorter regular workshops (non‐intensive format). The intended effect of this education program is to improve radiographers' ability to detect and describe abnormalities visualised on trauma radiographs.

## Methods/Design

### Study design

The Standard Protocol Items: Recommendations for Interventional Trials (SPIRIT) 2013 guidelines were used when preparing this study protocol.^20^ The study design is a multicentre, stratified (by years of experience) two group parallel‐arm single‐blind (assessor blinded) randomised controlled trial (Fig. 1). Participants will be allocated to one of the two groups: (1) intensive format of education or (2) non‐intensive format of education in a 1:1 ratio to examine whether either education delivery approach is superior to the other. Participants will undergo an assessment of their ability to interpret adult skeletal X‐rays, before education, at 1 week post‐intervention completion (primary time‐point) and at 12 weeks post‐intervention completion.

**Figure 1 jmrs264-fig-0001:**
[figure not shown]
Study design – randomised control trial.

### Ethics statement

The Human Research Ethics Committees of both the Metro South Hospital and Health Service (HREC/11/QPAH/172) and the Queensland University of Technology (1200000061) approved this research.

### Setting and participant recruitment

Radiographers will be recruited from three metropolitan hospital medical imaging departments in southeast Queensland. These hospitals were chosen as they each have a dedicated emergency‐imaging department. Radiographers eligible for inclusion in the study must be currently working in an emergency‐imaging department and willing to undertake either intensive or non‐intensive image interpretation training. Radiographers in the participating sites will be invited to participate in the study via email invitation. This will be achieved by sending the radiographer clinical educator at each of the sites an email asking them to forward the invitation to participate to all their radiographers who rotate through their emergency‐medical imaging department. Radiographers will be excluded from the study if they: have previously completed formal education in image interpretation or commenting (e.g. a master's degree that included image interpretation coursework); are not available to attend training at the potential scheduled times; or do not hold full registration as a radiographer with the national board. Accompanying the original email invitation will be a participant information sheet and a consent form. The participant information sheet provides potential participants with the necessary understanding for the motivation and procedures that underpin this study as well as further information to allow them to give informed consent. There will also be opportunity for potential participants to contact a member of the research team for further information or to ask further questions. The participant information sheet also includes details explaining that the education sessions will be held out of normal business hours. For example, the intensive education will be held on weekends and the non‐intensive education will be held in the evenings. Participants are encouraged to ensure they are available to attend all the education sessions. Participants will provide written informed consent and are free to withdraw this consent at any time. Written consent forms will be collected by a member of the research team prior to participation.

### Randomisation

Computerised random number generation will be used to generate the randomisation sequence by a researcher not otherwise involved in the recruitment or assessment of participants. Participants will be stratified into four bands by years of clinical experience (1–2; 3–5; 6–12; 13 years+) to minimise the risk of differences in experience levels between groups. Concealment of allocation will occur through use of numbered opaque envelopes containing the group allocation for each participant and stored in a locked filing cabinet until the time of allocation. After a participant has completed their baseline assessment, an intervention co‐ordinator will be permitted to access the envelope with the corresponding participant number and open the envelope to reveal allocation (to either the intensive format or non‐intensive format). The baseline assessment will involve participants completing the primary and secondary outcome measures. This assessment will be conducted at the participant's place of work and scheduled in consultation with the participant and their manager to ensure their attendance.

### Intervention

The standardised education intervention will be delivered in two formats: one group will receive intensive education (2‐day intensive format of delivery) and the other group will receive non‐intensive or more traditional education (sequential 90‐min tutorials delivered (at least) 1 week apart).

Both formats contain identical content in the same overall ‘education time’ covering appendicular and axial skeletal trauma. The educational program was originally developed to enhance junior emergency doctors' skills in interpreting trauma radiographs. This program has been refined to suit radiographers by the original developer. To cater for multiple learning styles, the program incorporates a blended learning environment combining two distinct modes, passive traditional classroom teaching and an interactive visual practical component.^21^ Within the two modes of learning, a number of learning aids are included to cater for different learning styles incorporating multisense, psychomotor and affective strategies.^22^, ^23^ The education program also integrates several original acronyms and mnemonics to assist the learner with memory retention and support them practising the skills learnt to build capability.

The program is divided into nine 90‐min workshops (see Table 1) including using a search strategy; how to structure findings, common traumatic pathology, normal variants and frequently missed abnormalities. Paediatric trauma is not covered in this education program, as the education program has been developed at a site that is not a paediatric (<14 years of age) centre. To standardise intervention delivery, the same facilitators, both of whom are members of the research team, experienced in image interpretation and facilitation of training, will deliver the courses (together). The facilitators are neither aware of the contents of the assessments nor involved with marking the assessments. Class size will be comparable for both formats. To facilitate learning opportunities and interactions within the education sessions, the size of each class will be kept to approximately 12 students.^24^, ^25^

**Table 1 jmrs264-tbl-0001:** Education intervention content outline

Workshop	Subject
1	General principles and strategy for interpretation of skeletal trauma
2	Hand, wrist and forearm
3	Face including mandible
4	Foot, ankle and tibia/fibula
5	Knee and distal femur
6	Pelvis and hips
7	Shoulder and humerus
8	Spine
9	Review of all content

To promote ongoing participation in the non‐intensive educational intervention, radiographers in this group will receive reminders prior to each weekly session via email. Furthermore, to promote completion of the education program for participants in both groups, this education program is eligible for accrual of continuing professional development points (equal to 13.5 h) recognised by the national registration board. A certificate of completion as evidence of accrual of the continuing professional development points will be provided to participants who complete the training.

### Outcome measures

#### Primary outcome measure

The primary outcome measure will be the Image Interpretation Test (IIT) assessment score, which has favourable evidence supporting its validity and reliability among radiographers.^26^ The development of this test has been described in detail in an earlier publication.^26^ This assessment involves participants examining a test bank of radiographic examinations (presented in random order) to try to identify abnormalities (and provide a descriptive comment when an abnormality is observed). The IIT assessment contains 60 examinations. It includes various appendicular and axial skeletal radiographs with a distribution of anatomical regions and proportion of abnormal cases that has been reported as consistent with a typical adult case mix from a hospital emergency department.^26^ This case mix was determined by conducting an audit of consecutive adult examinations over a 12‐month period. A description of this audit has been described previously.^26^ Participants in the trial will have their responses for each IIT examination (e.g. detection of normal or abnormal and description of abnormalities identified) scored by a blinded examiner. Two radiographers with postgraduate qualifications in image interpretation will serve as a panel of independent examiners to score and compare participant responses to the reference standard for each examination. The examiners will not be involved with the study design, conduct or education intervention (and blinded to group allocation and participant's identity). A reference standard has been created for each examination by a panel of experienced experts (two consultant radiologists and one consultant reporting radiographer).^26^ A novel rating scale has also been developed and validated in an earlier publication (Table 2).^26^ The examiners will be trained on how to use the rating scale by the site investigator (MN). They will be provided with a guide and worksheet to enable a consistent framework for marking. By using the rating scale, each examination in the IIT will be given a numerical value with a maximum total score of 3 and a minimum of 0. When marking assessments, discordant ratings will be discussed between the examiners until consensus reached.

**Table 2 jmrs264-tbl-0002:** Scoring criteria for each examination in the Image Interpretation Test

Criteria	Score
For radiographic cases with a traumatic abnormality	
Abnormality not detected	0
Abnormality detected, but not described correctly	1
Abnormality detected, description incomplete (but not incorrect)	2
Abnormality detected and correctly described in entirety	3
For radiographic cases with no traumatic abnormality	
False abnormality reported or described	0
Correct report of absence of any traumatic abnormality	3

To determine which format of delivery resulted in greater improvement and maintenance of image interpretation capability, the IIT will be completed prior to education commencement, 1 week after education completion and at 12 weeks post‐education completion for both formats. A 12‐week reassessment will provide an indication of whether there is difference in the maintenance of improvements observed at the first post‐intervention assessment. The 12‐week duration was also chosen so that a comparison could be made between the 12‐week post‐intensive format assessment, with the 1‐week post‐non‐intensive format assessment as these would be approximately the same number of weeks post‐intervention commencement (i.e. approximately 13 weeks). To help limit case recall bias at individual assessment points, each test bank of images will be presented in random order. The order of the cases will be determined by a computer‐generated randomisation sequence. To minimise the impact of post‐test discussion, participants will be asked not to discuss the cases within the test. This however could not be directly monitored or controlled by the investigators.

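### The intensive 12-week v non-intensive 1-week comparison is justified by a common 13 weeks since commencement, but if the nine workshops are weekly the two tests fall at about week 12 and week 9

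*Protocol article*

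**What the plan says.** Three statements in the protocol article bear on the timing.

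- **Primary outcome measure.** Both arms sit the Image Interpretation Test before teaching and again 1 and 12 weeks after their teaching ends. The first reason given for the 12-week test is to see whether gains are maintained. The second is to allow the intensive arm at 12 weeks to be compared with the non-intensive arm at 1 week, because "these would be approximately the same number of weeks post‐intervention commencement (i.e. approximately 13 weeks").
- **Intervention, description of the formats.** "The program is divided into nine 90‐min workshops". The non-intensive arm receives "sequential 90‐min tutorials delivered (at least) 1 week apart", with no upper limit on the spacing. For the other arm, "one group will receive intensive education (2‐day intensive format of delivery").
- **Intervention, promotion of attendance.** In the non-intensive arm, "radiographers in this group will receive reminders prior to each weekly session via email".

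The article does not give the length of the non-intensive course in weeks.

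**The concern.** Equal time since commencement is the only reason offered for this cross-time-point comparison, and one of two reasons for placing the later test at 12 weeks. The claim depends on how long the non-intensive course lasts. The only definite frequency in the article is weekly, and nine weekly sessions do not last long enough to bring the 1-week test to 13 weeks.

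If the sessions do run weekly, the intensive arm will have had about three more weeks of clinical practice, or of forgetting, when the two tests are compared. A difference between the arms, or the absence of one, would then be presented as time-matched when it is not.

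**Working it through.** **Inputs**
- Workshops: 9, hence 8 gaps from first to last (Intervention).
- Gap between non-intensive workshops, *g*: at least 7 days in the description of the formats; weekly in the sentence on reminders (both Intervention).
- Intensive course: 2 days, so it ends 1 day after it starts (Intervention).
- Tests: 7 and 84 days after the end of teaching (Primary outcome measure).
- Stated common time: about 13 weeks, or 91 days (Primary outcome measure).

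**Formulas, in days from the first teaching day**
- Non-intensive 1-week test = 8*g* + 7
- Intensive 12-week test = 1 + 84 = 85 days = 12.1 weeks

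**Trying to reproduce the stated 13 weeks**
- Intensive arm: 12.1 elapsed weeks. If the teaching week is counted as week 1, the test falls in week 13, which fits the article's figure.
- Non-intensive arm, weekly (*g* = 7): 8 × 7 + 7 = 63 days = 9.0 weeks. If the first session's week is counted as week 1, the test falls in week 10. Neither count gives 13.

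**Size of the mismatch at weekly spacing**
- 85 − 63 = 22 days, or 3.1 weeks.
- 22 / 63 = 35% more elapsed time in the intensive arm.
- By calendar-week counting: week 13 v week 10, 3 weeks.

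**Spacing that would give the stated match**
- To equal the intensive test: (85 − 7) / 8 = 9.75 days, a span of 78 days (11.1 weeks).
- To reach 13 weeks: (91 − 7) / 8 = 10.5 days, a span of 84 days (12 weeks).

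**Dependence on the average gap**

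| Average gap (weeks) | Non-intensive 1-week test (weeks) | Intensive 12-week test minus this (weeks) |
|---|---|---|
| 1 | 9.0 | +3.1 |
| 1.25 | 11.0 | +1.1 |
| 1.39 | 12.1 | 0.0 |
| 1.5 | 13.0 | −0.9 |
| 2 | 17.0 | −4.9 |

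Nine weeks is the earliest the non-intensive test can fall, so 3.1 weeks is the most by which it can precede the intensive test. With wider spacing the sign reverses.

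**The case against.** The best reply is that the section defining the intervention allows gaps longer than a week. Gaps averaging 9.75 to 10.5 days meet that minimum and put the non-intensive test at 12.1 to 13 weeks, so the definition and the stated match can both be true. The word weekly appears only in a sentence about reminders, and the 13-week figure is hedged twice as approximate. A condensed article may also leave the course calendar to the full protocol.

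Much of this stands. A reader might infer that the non-intensive test is fixed at week 9 and that 13 weeks is simply an arithmetic error. The article does not support that reading, because the minimum-spacing wording makes 9 weeks a lower bound. Nor is the lack of an upper limit on spacing a fault in itself.

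It does not remove the conflict. The article chooses to state an elapsed time and rests a comparison on it. The only definite frequency it gives yields 9 weeks, and the hedge does not absorb a shortfall of 3 weeks against the other arm or 4 against the stated figure. A span of 11 to 12 weeks for nine sessions would support the claim, but no such span is stated.

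It is also fair that the consequence is limited. The Statistical methods section does not name this comparison, and nothing in the article shows that three weeks would change test scores materially.

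**Conclusion.** The point holds conditionally. If the workshops are weekly, as the reminder sentence says, the two tests compared fall at about 9 and about 12 weeks after commencement, 22 days apart, and the equal-time justification fails. If they are spaced about 10 days apart on average, the justification holds but the weekly wording does not. The article's statements do not jointly yield the stated figure, and the direction of any mismatch turns on a span it does not give.

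The calculation assumes even spacing, or equivalently an average gap, and counts commencement from each arm's first teaching day.

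The primary comparison, 1 week after completion in each arm, is unaffected, as is the use of the 12-week test to study maintenance. No sample size or primary conclusion rests on the contrast. This is a minor-to-moderate correction.

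**What to change.** 1. Reconcile the two Intervention statements on spacing with the Primary outcome measure section by stating the planned first-to-ninth-workshop span of the non-intensive course.
2. If sessions are weekly, replace the 13-week figure with about 9 weeks (non-intensive) v about 12 weeks (intensive), and withdraw the claim of equal elapsed time.
3. In either case, record the date of each participant's first session and of each test. Report actual elapsed time since commencement by arm alongside this secondary contrast, and describe it as time-matched only if those times agree.

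Interpolating the intensive arm's score to the non-intensive arm's week is not a sound substitute. It assumes linear change between the 1-week and 12-week tests, which nothing in the article supports, and it mixes second and third sittings of the same test.

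The cost is a few sentences and the recording of dates, with no extra participants or assessments. The downside is small: a secondary contrast may lose its time-matched label.
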